## Abstract

**Rationale:**

Enteral nutrition is beneficial for stroke patients with oral intake difficulties. However, it is time consuming and may interfere with routine medical care. Therefore, there is a clinical benefit if enteral nutrition can be safely administered in a short time. Although our retrospective study showed the safety of rapid administration, it remains unclear whether rapid administration of enteral nutrition is as safe as conventional administration.

**Aim:**

The randomized study of Enteral Nutrition with Rapid versus conventional administration in acute stroke patients (Rapid EN trial) aims to clarify the safety of rapid feeding of enteral nutrition compared with conventional feeding.

**Methods and design:**

This is an investigator-initiated, multicenter, prospective, randomized, open-label, blinded end-point clinical trial. Eligible criteria include acute stroke patients who have difficulty with oral intake defined as severe altered consciousness (Japan Coma Scale 10–300) or modified water swallowing test <4. The target enrollment is 700 patients, with 350 patients receiving rapid enteral nutrition at a rate of 100 mL in 5 min (Rapid EN group) and 350 patients receiving conventional enteral nutrition at a rate of 100 mL in 30 min (Conventional EN group).

**Study outcome:**

The primary outcome is the incidence of one or more complications of vomiting or diarrhea or pneumonia within 7 days would be non-inferior in the rapid EN group compared to the conventional EN group. Secondary outcomes were total time spent on enteral nutrition within 7 days from enteral nutrition, the incidence of vomiting, diarrhea and pneumonia within 3 or 7 days, and the rate of favorable clinical outcome.

**Discussion:**

Since no previous reports have focused on the speed of administration, we felt it was necessary to prove the safety of rapid administration. If this study shows positive results, it will not only benefit patients, but also reduce the burden of medical care. We believe this study is novel and will be useful in clinical practice.

**Clinical trial registration:**

https://rctportal.niph.go.jp/s/detail/um?trial_id=UMIN000046610 Identifier UMIN000046610.

## Introduction

1

Malnutrition was observed in 6.1–62% of stroke patients. Nutritional assessments of older patients in rehabilitation and subacute hospitals after acute treatment revealed that 50.5% were malnourished (1), and these patients with malnutrition at the time of transfer had a lower rate of returning home (2, 3). Nutritional interventions in the acute phase after a stroke may prevent the increased infection risk associated with malnutrition and avoid rehabilitation delays due to weight loss and muscle weakness. Studies in the intensive care unit and on trauma patients during the acute phase have reported that early initiation of enteral nutrition (EN) reduces the incidence of infection and mortality (4, 5).

Early nutrition initiation effectively improves malnutrition, and EN is beneficial for patients with difficulties in oral intake. According to the most recent guidelines, in cases where severe dysphagia is expected to last >7 days, enteral tube feeding should be initiated within the first 72 h after stroke onset (6, 7). However, early initiation of EN is associated with risks, such as vomiting, diarrhea, and aspiration pneumonia (8). The recommended slow and diluted administration method to manage risk is time-consuming and may interfere with routine medical care. In addition, the effectiveness of slow and diluted administration is not clearly evident. The acute phase of stroke management requires time to spend on intravenous drip infusion, frequent imaging studies, and rehabilitation therapy; prolonged EN may interfere with these treatments. Therefore, safe administration of EN in a short time is clinically beneficial; conversely, the complication rate associated with rapid administration should be non-inferior to that of conventional administration.

Previous studies have demonstrated the potential for safe and rapid EN administration (9). We hypothesized that rapid EN administration is as safe as conventional administration. Therefore, we planned a multicenter trial to test this hypothesis.

## Methods

2

### Design

2.1

This randomized study of rapid EN versus conventional administration in acute stroke patients (Rapid EN Trial) is an investigator-initiated, multicenter, prospective, randomized, open-treatment clinical trial conducted between October 2020 and March 2024. The Institutional Review Board of each hospital approved this trial. All the enrolled patients and their relatives provided written informed consent. This trial was registered as a UMIN Clinical Trial (ID: 000046610). Figure 1 shows a flowchart of the trial design.

**Figure 1 fig1:**
[figure not shown]
Outline of the study.

### Participants

2.2

Patients aged ≥20 years who developed stroke within 7 days from onset, had difficulty with oral intake and could raise their head more than 30 degrees represented the target population in the Rapid EN trial. Patients who had difficulty with oral intake were defined as having severely altered consciousness (JCS 10–300), or modified water swallowing test (MWST) (10) <4. Patients with obstructive gastrointestinal tract disease unfit for enteral feeding were excluded. Table 1 shows the inclusion and exclusion criteria.

**Table 1 tab1:** Inclusion and exclusion criteria.

Inclusion criteria
∙Age ≥ 18 years at the time of giving informed consent. ∙Clinical diagnosis of acute ischemic stroke within 7 days from onset. ∙Patients who can be randomized within 72 h from admission. ∙Patients who have difficulty with oral intake are defined as severely altered consciousness (JCS 10–300) or modified water swallowing test <4. ∙Patients who can raise their head more than 30 degrees. ∙Written informed consent by the patient or next of kin.
Exclusion criteria
∙Obstructive diseases of the gastrointestinal tract. ∙Pregnancy or possibility of pregnancy. ∙patients with an expected life expectancy of 90 days or less. ∙Patients who are deemed by the investigator or sub-investigator to be unsuitable for participation in this study.

JCS, Japan Coma Scale.

### Randomization

2.3

Eligible patients are randomized into a 1:1 ratio using a web-based data management system to undergo either rapid administration (rapid EN group) or conventional administration (conventional EN group) of EN within 72 h of admission. Using a minimization algorithm, we balanced the number of patients in the two treatment groups at each hospital.

### Treatment or intervention

2.4

All the patients received EN using dobhoff tube, NG tube or PEG tube. The enteral feeding dose was 100 mL for the first 3 days and was determined by each institution for each patient for 4–7 days. EN was administered at a rate of 100 mL in 5 min for 7 days in patients randomized to the Rapid EN group and 100 mL in more than 30 min in patients randomized to the Conventional EN group. The type of enteral nutritional supplement is unspecified and freely chosen by each patient.

### Clinical assessments

2.5

Performances at baseline, three complications of enteral nutrition, including vomiting, diarrhea, and pneumonia, for 3–7 days from the start of EN, location of stroke, the length of hospital stay and clinical outcomes will be assessed by a third independent observer blinded to the group assignment. Vomiting was defined as one or more episodes associated with EN initiation. Diarrhea was defined as a score of 6 or 7 on the Bristol Stool Scale (11), persisting for more than 2 days. Pneumonia was defined as physician-observed pneumonia based on imaging and clinical status. Clinical outcomes were assessed using the modified Rankin scale (mRS) score (range, 0 [no symptoms] to 6 [death]) (12); favorable clinical outcomes were defined as an mRS score of 0–2 at 90 days after stroke onset.

### Primary outcome

2.6

The primary outcome is the incidence of one or more complications (vomiting, diarrhea, or pneumonia) within 7 days of EN initiation for comparing non-inferiority in the rapid EN and conventional EN groups.

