### Secondary outcomes

2.7

Secondary outcomes were total time spent on EN, incidence of vomiting, diarrhea, and pneumonia within 3 and 7 days of EN, incidence of one or more of the three complications in patients with ischemic or hemorrhagic stroke, and rate of favorable clinical outcome. The efficacy and safety endpoints are presented in Table 2.

**Table 2 tab2:** Primary and secondary outcomes.

Primary outcome
∙Incidence of vomiting or diarrhea or pneumonia within 7 days of initiation of enteral nutrition (non-inferiority).
Secondary outcomes
∙Total time spent on enteral nutrition within 7 days of initiation of enteral nutrition (hours).
∙Incidence of vomiting within 7 days of initiation of enteral nutrition.
∙Incidence of diarrhea within 7 days of initiation of enteral nutrition.
∙Incidence of pneumonia within 7 days of initiation of enteral nutrition.
∙Incidence of vomiting or diarrhea or pneumonia within 3 days of initiation of enteral nutrition (non-inferiority).
∙Incidence of vomiting within 3 days of initiation of enteral nutrition.
∙Incidence of diarrhea within 3 days of initiation of enteral nutrition.
∙Incidence of pneumonia within 3 days of initiation of enteral nutrition.
∙Incidence of vomiting or diarrhea or pneumonia within 7 days of initiation of enteral nutrition in ischemic stroke patients (non-inferiority).
∙Incidence of vomiting or diarrhea or pneumonia within 7 days of initiation of enteral nutrition in intracerebral hemorrhage and subarachnoid hemorrhage patients (non-inferiority).
∙Favorable outcome defined as mRS score 0–2 at 90 days after stroke onset.

mRS, modified Rankin Scale.

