### Statistical analyses

2.11

An intention-to-treat (ITT) analysis will be applied according to the consolidated standards of Reporting Trials (14). As needed, an analysis will be performed on the per-protocol set as a sensitivity analysis of the ITT results. Patient demographic data will be analyzed descriptively. Categorical variables will be assessed using the chi-square test or Fisher’s exact test. In contrast, continuous variables will be assessed using Student’s *t*-test or Wilcoxon rank-sum test, as appropriate. The primary outcome is the proportion of patients with one or more complications at 7 days between the rapid EN and conventional EN groups, as analyzed using univariate logistic regression analysis. Multivariate logistic regression analysis adjusted for potential confounders was performed as a sensitivity analysis. The primary outcome’s odds ratio (OR) will be calculated with the corresponding 95% confidence interval (CI). This clinical trial aimed to demonstrate the non-inferiority of Rapid EN over Conventional EN. If noninferiority is statistically demonstrated for the primary endpoint and the incidence in the rapid EN group is lower than that in the conventional EN group, superiority tests will be implemented. All statistical tests are one-sided, and *p* < 0.025 are considered statistically significant.

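### No listed outcome compares death between the arms, and an early death without a recorded complication has no primary event

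*Protocol article*

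**What the plan says.** The Abstract states that the trial "aims to clarify the safety of rapid feeding of enteral nutrition compared with conventional feeding". Section 2.6 defines the primary outcome as "the incidence of one or more complications (vomiting, diarrhea, or pneumonia) within 7 days of EN initiation". Section 2.7 says "The efficacy and safety endpoints are presented in Table 2". That table has 1 primary and 11 secondary entries, and none is death at any time point.

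Death enters only through the mRS in section 2.5, whose scale is given as "range, 0 [no symptoms] to 6 [death". The endpoint built on it is a two-class split: "favorable clinical outcomes were defined as an mRS score of 0–2 at 90 days after stroke onset".

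On the population, section 2.2 admits patients with "severely altered consciousness (JCS 10–300") or with a modified water swallowing test below 4. Table 1 excludes "patients with an expected life expectancy of 90 days or less".

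On analysis, section 2.11 says "An intention-to-treat (ITT) analysis will be applied", with univariate logistic regression for the primary proportion. Section 2.10 provides an independent safety board, immediate reporting of unexpected events, and analysis of the safety endpoints after 100 and 400 patients. It does not name mortality.

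**The concern.** Death ends the period in which vomiting, diarrhea or pneumonia can be observed. The component definitions in section 2.5 make this practical rather than theoretical. Diarrhea has to persist for more than 2 days, so a patient who dies on day 1 or 2 of feeding cannot meet it. Pneumonia rests on imaging and clinical status, so a death before imaging may leave it unrecorded. With a binary outcome analysed in all randomized patients, such a patient stays in the denominator without an event.

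In a non-inferiority trial of safety this works in the unfavourable direction: extra complication-free deaths in the rapid arm would lower that arm's observed complication rate. Section 2.11 adds a superiority test if the rapid arm's rate is lower, so the same mechanism could feed that claim too. At 90 days, a difference in mortality could also go unseen in every listed outcome if it lay within mRS 3–6.

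**Working it through.** The article states no figure for death, so there is none to reproduce. The check has two parts: the definitions side by side, then illustrative arithmetic on assumed death rates.

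**Definitions.** The primary composite has three components and death is not one of them. Of the 11 secondary outcomes, 10 concern feeding time or the same three complications. The eleventh is mRS 0–2, where death (6) falls in the same class as mRS 3, 4 and 5. No between-arm comparison of death is listed.

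**Inputs.** From section 2.8: conventional 14/26 = 53.8%, rapid 22/45 = 48.9%, margin 5% (read as absolute points), 350 per arm, one-sided 0.025. Assumed: the share *d* of each arm that dies by day 7 without a complication. The complication rate *p* applies to the remaining patients.

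**Formulas.** Observed risk with such deaths as non-events: p(1 − d). Risk with them counted as events: p(1 − d) + d. The difference (rapid minus conventional) therefore moves by exactly d(rapid) − d(conventional).

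**Small excess.** An excess of 1 to 2 points is 350 × 0.01 = 3.5 to 350 × 0.02 = 7 patients. The shift is 1 to 2 points, which is 1/5 = 20% to 2/5 = 40% of the margin. The planned distance to the margin also includes the expected advantage of rapid feeding: 5 + (53.8 − 48.9) = 9.9 points. Against that distance the shift is about 10% to 20%.

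**Wider range (all death rates assumed).**

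| Complication-free deaths, conventional / rapid | Complication rate among the rest | Difference, deaths as non-events | Difference, deaths as events |
|---|---|---|---|
| 2% / 2% | planned rates | −4.9 | −4.9 |
| 2% / 5% | planned rates | −6.3 | −3.3 |
| 5% / 10% | planned rates | −7.2 | −2.2 |
| 2% / 8% | planned rates | −7.8 | −1.8 |
| 2% / 8% | 53.8% in both arms | −3.2 | +2.8 |

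Last row worked: 53.8% × 0.92 − 53.8% × 0.98 = −3.2 points; adding 8 − 2 = 6 points gives +2.8. The sign reverses, but only under a large assumed excess. With equal deaths (first row) nothing changes.

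**mRS.** Suppose mRS 0–2 were 15% in both arms and 90-day death 15% versus 20%. The listed outcome would show 15 − 15 = 0 while mortality differed by 20 − 15 = 5 points. The zero is built into the assumption, so this shows only that the pattern is possible.

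**The case against.** The strongest objection is to the mechanism. The bias needs excess deaths in the rapid arm among patients with none of the three complications. The harms that the article expects from feeding are those three, and a single episode of vomiting already makes an event, so a feeding-related death that follows vomiting or pneumonia is already counted. Deaths from the stroke itself should be balanced by randomization. This stands: it makes a large bias less likely. It does not supply a comparison of death, and it relies on the complication being recorded before the patient dies.

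A reader might infer that the plan scores an early death as a safety success. The article states no such rule. The classification follows from the definition, and an analysis plan that is not shown may handle these deaths differently. The endpoint list itself, however, is given item by item.

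A reader might also infer that mRS 0–2 hides death by treating it as a good result. It does not: death is unfavourable. The loss is that it cannot be told apart from mRS 3–5. Nor do the documents show how many patients would reach mRS 0–2. A failed swallowing test alone qualifies for entry, and patients must be able to raise the head more than 30 degrees.

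The safety board and the exclusion of short life expectancy are real safeguards. But an expected survival is a prediction, and deaths in deeply comatose patients may not be classed as unexpected.

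**Conclusion.** The point holds as a cheap improvement to the stated endpoint list. A claim that rapid feeding is as safe as conventional feeding would be made without any listed comparison of death between the arms, and the primary definition gives no event to a complication-free early death. The direction of any resulting bias is clear: it favours the rapid arm if such deaths are in excess there. The size cannot be derived. An assumed excess of 1 to 2 points shifts the risk difference by 1 to 2 points against the 5-point margin, and equal deaths leave it essentially unchanged. The documents do not support the stronger conclusion that the primary comparison is biased or that the trial would miss an actual mortality excess. They contain no death rate and no evidence that deaths would differ by arm.

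**What to change.** Add all-cause death at 7 days and at 90 days, by arm, to Table 2 as safety outcomes. State how a death before day 7 enters the primary analysis. Pre-specify a supportive sensitivity analysis of the primary comparison in which vomiting, diarrhea, pneumonia or death within 7 days of starting EN is the event.

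This analysis should not become a second condition for the non-inferiority claim. At the planning rates and one-sided 0.025, the standard error of the difference with 350 per arm is √[(0.538 × 0.462 + 0.489 × 0.511)/350] = 0.0377. Power is then Φ(0.0996/0.0377 − 1.96), about 75%, before any death is counted. With deaths included it would be 74.4% at an assumed 2% / 2% and 59.8% at 2% / 5%. A second requirement could only lower the chance of success further.

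The cost is small: one extra analysis and two table rows. The 90-day mRS already codes death, and patients are followed for complications through day 7, so vital status at day 7 should be available (an assumption). The drawbacks are a composite less specific to feeding and limited power for death alone. For 15% versus 20% (assumed) with 350 per arm, the standard error is √[(0.15 × 0.85 + 0.20 × 0.80)/350] = 0.0287, z = 0.05/0.0287 = 1.74, and power is about 41%. The death outcomes should therefore be reported as estimates with confidence intervals, and a non-significant difference should not be read as evidence of equal mortality.

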### Secondary outcomes

2.7

Secondary outcomes were total time spent on EN, incidence of vomiting, diarrhea, and pneumonia within 3 and 7 days of EN, incidence of one or more of the three complications in patients with ischemic or hemorrhagic stroke, and rate of favorable clinical outcome. The efficacy and safety endpoints are presented in Table 2.

**Table 2 tab2:** Primary and secondary outcomes.

Primary outcome
∙Incidence of vomiting or diarrhea or pneumonia within 7 days of initiation of enteral nutrition (non-inferiority).
Secondary outcomes
∙Total time spent on enteral nutrition within 7 days of initiation of enteral nutrition (hours).
∙Incidence of vomiting within 7 days of initiation of enteral nutrition.
∙Incidence of diarrhea within 7 days of initiation of enteral nutrition.
∙Incidence of pneumonia within 7 days of initiation of enteral nutrition.
∙Incidence of vomiting or diarrhea or pneumonia within 3 days of initiation of enteral nutrition (non-inferiority).
∙Incidence of vomiting within 3 days of initiation of enteral nutrition.
∙Incidence of diarrhea within 3 days of initiation of enteral nutrition.
∙Incidence of pneumonia within 3 days of initiation of enteral nutrition.
∙Incidence of vomiting or diarrhea or pneumonia within 7 days of initiation of enteral nutrition in ischemic stroke patients (non-inferiority).
∙Incidence of vomiting or diarrhea or pneumonia within 7 days of initiation of enteral nutrition in intracerebral hemorrhage and subarachnoid hemorrhage patients (non-inferiority).
∙Favorable outcome defined as mRS score 0–2 at 90 days after stroke onset.

mRS, modified Rankin Scale.

### Sample size estimates

2.8

A previous observational study (9) showed that the proportion of patients with one or more complications, defined as vomiting, diarrhea, or pneumonia, was 22/45 (48.9%) in the rapid EN group and 14/26 (53.8%) in the conventional EN group. Based on previous reports, the non-inferiority margin was defined as a minimum clinically important difference (MCID) of 5% in the outcome (13). According to those results, we estimated that 622 patients would need to be enrolled to detect non-inferiority of the rapid EN group compared with the conventional EN group, based on a 1-sided α level of 0.025 and a power of 0.80. In total, 700 patients (350 per intervention and control group) were recruited, accounting for possible treatment failures, protocol violations, and dropouts.

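### The stated 80% power is not delivered at one-sided 0.025: with 700 patients it is about 75% if rapid feeding is truly 5 points better, and about 26% if it is only as safe

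*Protocol article*

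**What the plan says.** Section 2.8 of the protocol article takes its planning rates from an earlier observational study, where the proportion with at least one complication "was 22/45 (48.9%) in the rapid EN group and 14/26 (53.8%) in the conventional EN group". On the margin it says that "the non-inferiority margin was defined as a minimum clinically important difference (MCID) of 5% in the outcome". It continues: "According to those results, we estimated that 622 patients would need to be enrolled to detect non-inferiority of the rapid EN group", "based on a 1-sided α level of 0.025 and a power of 0.80". The 622 is then raised to 700 (350 per arm) for treatment failures, protocol violations and dropouts. Section 2.11 repeats the 0.025 level for one-sided tests.

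The Introduction gives the aim in other terms: "We hypothesized that rapid EN administration is as safe as conventional administration". The article nowhere says that the sample size depends on rapid feeding being better than conventional feeding.

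**The concern.** There are two problems with one stated power figure.

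- **The planning effect is a benefit.** Entering 48.9% against 53.8% puts the assumed truth 4.96 points on the favourable side of zero. The distance to the margin becomes 9.96 points, about twice the margin. Sample size varies with the inverse square of that distance, so the assumption dominates the calculation.
- **The alpha does not match.** 622 appears to come from a looser alpha than the one stated. The 80% is then not reached even if the benefit is real.

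What is at stake is how the primary result is read. A reader told that power is 80% will expect the trial to show non-inferiority if rapid feeding is no worse. If the two feeding rates are truly equal, it would fail to do so about three times in four.

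**Working it through.** **Inputs** (all from 2.8 unless noted)

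- Rapid: pR = 22/45 = 0.4889. Conventional: pC = 14/26 = 0.5385. Difference pR - pC = -0.0496.
- Margin M = 0.05, read as an absolute risk difference (assumption).
- One-sided alpha 0.025 (z = 1.960; also in 2.11), power 0.80 (z = 0.8416), allocation 1:1 (2.3).
- 622 calculated (311 per arm), 700 planned (350 per arm).

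**Step 1. Reproduce 622.**

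n per arm = [pR(1-pR) + pC(1-pC)] × (z_alpha + z_power)² / (M + pC - pR)²

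Variance sum = 0.2499 + 0.2485 = 0.4984. Distance = 0.05 + 0.0496 = 0.0996.

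- One-sided 0.025: 0.4984 × 7.849 / 0.0996² = 394.6, so 395 per arm, **790** in total.
- One-sided 0.05: 0.4984 × 6.183 / 0.0996² = 310.8, so 311 per arm, **622** in total.

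The plan's figure is matched exactly at one-sided 0.05 and not at the stated 0.025. At 0.025, the variants tried with the observed rates (pooled variance, rounded rates, continuity correction, Farrington-Manning, an equivalent odds-ratio margin, 45:26 allocation) gave 780 to 852. Equal rates gave 3,122 to 3,140. The match at 622 therefore indicates that the 4.96-point benefit was entered and that the margin is absolute.

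**Step 2. Power at the stated alpha.**

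Power = Φ[(M - (pR - pC))/SE - 1.960], with SE = √{[pR(1-pR) + pC(1-pC)]/n}.

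For 350 per arm:

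- Assumed benefit: SE = 0.0377; 0.0996/0.0377 = 2.639; Φ(0.679) = 0.751.
- Half the benefit (pC = 0.5385, pR = 0.5137): Φ(0.022) = 0.509.
- No difference (both 0.5385): 0.05/0.0377 = 1.327; Φ(-0.633) = 0.263.

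| True difference (rapid minus conventional) | 700 evaluable | 622 evaluable |
|---|---|---|
| -4.96 points | 75% | 70% |
| -2.48 points | 51% | 46% |
| 0 | 26% | 24% |

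With both rates at 48.9%, the last row is also 26% and 24%. Reaching 80% at one-sided 0.025 would take a true benefit of about 5.6 points with 700 patients, or 6.2 points with 622.

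The alpha mismatch alone does not explain the low power under equality. At one-sided 0.05 with 700 patients it is still only 37-38%. For 80% power under equal rates at one-sided 0.025, n = 2 × 0.2485 × 7.849 / 0.05² = 1,560.5, so 1,561 per arm.

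**Step 3. What must be observed to pass.**

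With 350 per arm, the 95% CI half-width is 1.96 × 0.0377 = 0.0739, or 7.4 points. The upper limit stays below 5 only if the observed difference is below 5 - 7.4 = -2.4 points. Identical observed rates would fail.

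**Step 4. Support for the assumed benefit.**

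SE in the observational study = √(0.2499/45 + 0.2485/26) = 0.123. The 95% Wald CI is -4.96 ± 1.96 × 12.3, or -29.1 to +19.1 points. The 71 patients are compatible with no benefit, or with an excess well beyond the margin.

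**The case against.** **A favourable planning value is legitimate.** True differences of 0 and -5 points both lie in the non-inferiority alternative, and the Introduction's wording can be read as a lay statement of non-inferiority. This stands. A reader might infer that the 80% belongs to a different hypothesis from the one tested, but the documents do not support that. The benefit is an optimistic planning value, and the objection is that it is not named as one.

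**The rates are printed.** A reader can see both rates and their denominators and work out the assumption. That is partly fair. It does not rescue the stated power, which does not follow from those rates at the stated alpha.

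**The margin scale is not given.** Section 2.11 analyses the primary outcome by logistic regression with an odds ratio, so the absolute reading is an assumption. The exact match at 622 favours it. Converting the margin to an equivalent odds ratio (1.226) gives 780 at one-sided 0.025 and 614 at 0.05, so the mismatch remains.

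**Some consequences are not errors.** Section 2.11 allows superiority testing under this condition: "If noninferiority is statistically demonstrated for the primary endpoint and the incidence in the rapid EN group is lower than that in the conventional EN". At these rates any non-inferior result already meets it, but a redundant condition does no harm. The article also nowhere equates a failed non-inferiority test with harm, so that misreading is a risk and not something the plan says.

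**Recruitment is described in the past tense.** That argues against adding patients. It does not argue against correcting the stated power.

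**Conclusion.** The stated power is wrong as written. At one-sided 0.025 it is about 75% with 700 evaluable patients (70% with 622) if rapid feeding is truly 4.96 points better, and about 26% (24%) if the rates are equal. A tempting reading is that the 80% holds provided rapid feeding is about 5 points better. The figures do not support it, because the 80% is reached at that benefit with 622 patients only at one-sided 0.05.

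The conclusion rests on an absolute 5-point margin, common rates between 48.9% and 53.8% for the equality case, the normal approximation, and all counted patients being evaluable. It should be corrected because it governs how an unsuccessful primary result is understood. It does not invalidate the test, the margin or the enrolment.

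**What to change.** In 2.8, keep enrolment as it is and replace the 80% claim. Possible wording: *The calculation assumes a true complication rate 4.96 percentage points lower with rapid feeding, taken from 71 observational patients; the figure of 622 corresponds to a one-sided alpha of 0.05. At one-sided 0.025 with a 5-point absolute margin, power with 700 (622) evaluable patients is 75% (70%) at that benefit, 51% (46%) at half of it and 26% (24%) if there is no difference. At these rates with 350 per arm, non-inferiority requires an observed rate about 2.4 points lower with rapid feeding.*

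All three power values must use the same alpha. Printing 51% and 26% beside an uncorrected 80% would mix one-sided 0.025 with 0.05. The sponsor should confirm the margin scale before adopting the text.

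Optionally, add to 2.11 that a failed non-inferiority test whose confidence interval for the difference includes 0 will be reported as inconclusive.

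The cost is a few sentences and a less favourable stated power. No patients, tests or margin change.

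### The 622 patients in section 2.8 do not follow from its stated inputs: one-sided 0.025 with 80% power needs 790 evaluable, and the planned 700 give about 75% power

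*Protocol article*

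**What the plan says.** Section 2.8 (Sample size estimates) takes its event rates from an earlier observational study, in which the proportion with at least one complication "was 22/45 (48.9%) in the rapid EN group and 14/26 (53.8%) in the conventional EN group". On the margin it says that "the non-inferiority margin was defined as a minimum clinically important difference (MCID) of 5% in the outcome". From these it concludes: "we estimated that 622 patients would need to be enrolled to detect non-inferiority of the rapid EN group compared with the conventional EN group". The error rate and power behind that figure are given in the same sentence; the estimate is described as "based on a 1-sided α level of 0.025 and a power of 0.80". The target is then raised to 700, 350 per arm, to allow for losses and departures from protocol; no loss rate is given. Section 2.3 sets 1:1 allocation.

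Section 2.11 (Statistical analyses) uses the same error rate for the analysis: "All statistical tests are one-sided", with significance at p below 0.025, and the primary odds ratio is to be reported with a 95% confidence interval.

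**The concern.** Section 2.8 prints every input that the calculation needs, so its result can be checked from the page. With those inputs the required number is well above 622, and also above 700, before any patient is lost. The increase from 622 to 700 is presented as a reserve for losses, but 700 is 90 short of the requirement (790 − 700).

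What is at stake is the power claim for the primary outcome of a trial whose purpose is to establish safety. If non-inferiority is not shown, readers will judge that result against a stated 20% risk of missing true non-inferiority. Under the plan's own rates the risk is about 25% with everyone analysed, and about 30% if losses bring the analysed number down to 622.

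**Working it through.** **Inputs**
- Rapid EN rate p_R = 22/45 = 0.48889 (section 2.8)
- Conventional EN rate p_C = 14/26 = 0.53846 (section 2.8)
- Margin M = 0.05 (section 2.8), read as an absolute risk difference; this is an assumption, because the text says only 5% in the outcome
- One-sided alpha 0.025 (sections 2.8 and 2.11), power 0.80 (section 2.8), allocation 1:1 (section 2.3)

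**Formula (unpooled variance)**

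n per arm = (z_α + z_β)² × [p_R(1 − p_R) + p_C(1 − p_C)] / (M + p_C − p_R)²

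- Variance term: 0.24988 + 0.24852 = 0.49840
- Distance to the margin: 0.05 + 0.04957 = 0.09957; squared, 0.009915

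**Reproducing 622**
- One-sided 0.05, power 0.80: (1.645 + 0.842)² = 6.183, so n = 310.8, rounded up to 311 per arm, **622 in total**
- One-sided 0.025, power 0.70: (1.960 + 0.524)² = 6.172, so n = 310.3, rounded up to 311 per arm, **622 in total**

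Both match exactly.

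**With the stated inputs**
- One-sided 0.025, power 0.80: (1.960 + 0.842)² = 7.849, so n = 394.6, rounded up to 395 per arm, **790 in total**

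**Does the choice of method explain the gap?** Totals at one-sided 0.025 and 80% power:

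| Method | Total |
|---|---|
| Unpooled | 790 |
| Farrington-Manning | 790 |
| Pooled variance | 792 |
| Arcsine | 786 |
| Log odds ratio, margin converted at the control rate | 780 |
| Continuity-corrected | 830 |
| Unpooled, rates rounded to 48.9% and 53.8% | 800 |
| Unpooled, rates rounded to 49% and 54% | 784 |

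The range is 780 to 830. To obtain 622 at the stated alpha and power, the margin would have to be about 6.3 points instead of 5.

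**Power at one-sided 0.025**

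Power = Φ(0.09957 / SE − 1.960), with SE = √(0.49840 / n per arm)
- 311 per arm: SE = 0.04003; 2.487 − 1.960 = 0.527; power **70.1%**
- 350 per arm: SE = 0.03774; 2.639 − 1.960 = 0.679; power **75.1%**

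**The case against.** The strongest objection is that the size of the error should not be inflated. With all 700 analysed, the plan's own rates give about 75% power, 5 points below the claim. The final test at one-sided 0.025 keeps its error rate, so a positive non-inferiority result would be as valid as planned. Both statements are right. They limit the harm to a misstated power and a higher chance of an inconclusive trial; they do not make 622 correct.

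It can also be objected that section 2.8 does not say on which scale the 5% margin applies, while 2.11 plans an odds ratio. That is fair, and the absolute reading has to be declared as an assumption. It does not rescue the figure: with the margin converted to the log-odds-ratio scale the total is 780.

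Three stronger readings are tempting, and the document does not support them.
- A reader might infer that 622 was computed at one-sided 0.05. That is one of two exact matches, the other being 70% power at the stated 0.025. It also depends on the unrounded fractions: with 48.9% and 53.8%, one-sided 0.05 gives 630. The calculation itself is not shown, so the cause stays open.
- A reader might fear that the analysis will be relaxed to a 90% interval to fit 622. Nothing points that way; 2.8 and 2.11 both fix one-sided 0.025, and 2.11 specifies a 95% interval.
- A reader might set the assumed 4.96-point advantage against the Introduction, which says "We hypothesized that rapid EN administration is as safe as conventional administration", and conclude that the design should have been powered for equal rates. That wording is ordinary for a non-inferiority trial, and 2.8 openly gives the rates and their observational source. How sensitive power is to this assumption is a fair separate question, but it is not part of the arithmetic error.

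**Conclusion.** The point holds as an internal inconsistency in section 2.8: 622 patients, one-sided 0.025 and 80% power cannot all be true with the printed rates and margin. The stated alpha and power need 790 evaluable patients, 168 more than 622 (27%). At the alpha that the trial will use, power is about 70% with 622 analysed and about 75% with 700.

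This rests on an absolute 5-point margin, 1:1 allocation, and true rates equal to those observed in the earlier study, that is, rapid feeding better by 4.96 points. The shortfall does not depend on the choice among the usual formulas. Which input was wrong cannot be settled from the document.

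**What to change.** Correct section 2.8 to say that, at one-sided 0.025 and with a margin of 5 percentage points on the absolute risk difference, 80% power needs 790 evaluable patients; and that the planned 700 give about 75% power if all are analysed and about 70% if losses leave 622, assuming rapid EN is truly 4.96 points better. Leave the 0.025 threshold in 2.11 unchanged: altering alpha in 2.8 to match 622 would only move the contradiction to 2.11.

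Optionally, add one sensitivity figure. If both true rates are 53.8%, then with 350 per arm SE = √(2 × 0.24852 / 350) = 0.03768, and power = Φ(0.05 / 0.03768 − 1.960) = Φ(−0.633), about 26%.

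The cost is a change of wording and numbers in one section, and a stated power that looks less favourable. Restating the power needs no extra patients. If the sponsor wants to keep the 80% claim instead, the evaluable target has to rise to 790, with the allowance for losses added on top.
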